## 9.4 SAE Reporting

Any AEs which fall under the definition of a SAE will be reported to the Chief Investigator or designated person within 24 hours, to be reviewed for relatedness and expectedness. However, hospitalisations for elective treatment of a pre-existing condition do not need reporting as SAEs.

Reports of related and unexpected SAEs (in the opinion of the Chief Investigator or designated person) will be reported to the REC within 15 days of the CI and/or central trial team becoming aware of the event. The Chief Investigator will also notify the Sponsor of all study SAEs.

Any pregnancy occurring during the study will result in the immediate discontinuation of the participant and the Sponsor should be notified within 24 hours so appropriate follow-up is conducted. Pregnancy itself is not an AE.

All SAEs will be recorded in the Citrus platform and any concerns raised immediately with the CI and may be tabled for discussion at the regular Trial Management Group meeting or referred to an independent Trial Steering Committee (TSC) for review.

## 9.5 Expectedness

We do not anticipate any serious adverse events due to the digital intervention, data collection or the focus groups..

The adverse events described below are expected to occur in this participant population and will not be classified or reported as SAEs unless felt to be directly related to the study intervention or qualitative work. This will be judged by the CI and ratified by the TSC.

- Fluctuation in self reports of severity of tinnitus and mood relating to this.

There are no known side effects relating to CBT, but as tinnitus can be a psychologically distressing condition patients will be made aware that they need to seek medical attention from the GP or other services available to them (such as 111, Accident & Emergency etc) in the event that their psychological state deteriorates, e.g., they develop suicidal ideation.

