## 14.3 Study Committees

A Trial Steering Committee (TSC) and Trial Management Group (TMG) will be appointed. The responsibilities of each group are as follows:

TSC- to review the safety data and to review and monitor the accruing data to ensure the rights, safety and wellbeing of the trial participants. They will make recommendations about how the study is operating and any ethical or safety issues. This Committee will also take on the role of a Trial Steering Committee, and so act as a single oversight committee meeting at least bi-annually.

Trial Management Group (TMG)- is responsible for the day-to-day running of the trial, including monitoring all aspects of the trial and ensuring that the protocol is being adhered to. It will include the Lindus Health Clinical Operations Team, Medical Lead and Product Manager working closely with the CI and Sponsor and will meet weekly in the first instance. After the initial weekly meetings, the TMG will meet on a regular basis, such as monthly or bi-monthly, to discuss study progress and address any issues that may arise.

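### Section 9.5 makes SAE status of tinnitus-related mood events depend on causality, with no seriousness limit, which contradicts sections 9.1 and 9.4

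*Protocol*

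**What the plan says.** **Seriousness (Protocol 9.1).** An event is serious because of its outcome: death, threat to life, hospital admission, lasting disability, birth defect, or an important medical event on medical judgement. Cause is not part of the definition.

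**SAE handling (9.4).** "Any AEs which fall under the definition of a SAE will be reported to the Chief Investigator or designated person within 24 hours", and the review of relatedness and expectedness comes after that report. "The Chief Investigator will also notify the Sponsor of all study SAEs". SAEs are also recorded in the trial's data platform and may be referred to the TSC. SAEs that are both related and unexpected, in the view of the CI or a designate, "will be reported to the REC within 15 days of the CI and/or central trial team becoming aware of the event".

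**Exemption (9.5).** Events expected in this population "will not be classified or reported as SAEs unless felt to be directly related to the study intervention or qualitative work". The list has a single entry: "Fluctuation in self reports of severity of tinnitus and mood relating to this". On the relatedness decision, "This will be judged by the CI and ratified by the TSC". Section 14.3 has the TSC "act as a single oversight committee meeting at least bi-annually".

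**Relatedness (9.2 and 9.3).** Section 9.2 treats *possibly*, *probably* and *definitely* all as related. Section 9.3 sends to the REC those AEs that the site PI judges to be caused by the trial intervention. It applies no expectedness filter and gives no deadline. AEs are collected from randomisation to the 3-month contact.

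**The concern.** Sections 9.1 and 9.4 follow the usual order: decide seriousness by outcome, report, then assess cause. Section 9.5 reverses that order for one class of event. The event must be felt to be directly related before it can be an SAE, yet 9.4 assesses relatedness only once an SAE has been reported. The rule is circular, and the two sections give opposite answers for the same event.

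Deterioration in psychological state is a harm the protocol itself foresees: 9.5 tells participants to seek care for it and 9.6.1 monitors for it. Under 9.4, the prompt CI report, Sponsor notification and SAE recording all depend on SAE status. A serious event in this class could lose them through a causality judgement made in an open-label trial.

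**Working it through.** No arithmetic applies; the check sets the clauses side by side.

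**Step 1: does the exemption change anything?** A change in tinnitus or mood that does not meet 9.1 is not an SAE with or without 9.5. The exemption therefore has effect only on events that would otherwise meet 9.1, and 9.5 gives no upper limit that takes serious events back out of it.

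**Step 2: follow one event.** Take an event that meets 9.1 and is described as tinnitus-related mood change.

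| Judgement on cause | 9.1, 9.2 and 9.4 alone | With 9.5 applied |
|---|---|---|
| Unrelated | SAE: CI within 24 hours, Sponsor notified, recorded as SAE; no REC report | Not an SAE; collected as an AE to 3 months |
| *Possibly* | Related SAE; REC within 15 days if unexpected | Unclear whether this counts as directly related; if not, as the row above |
| Directly related | Related SAE; REC within 15 days if unexpected | SAE, but already listed as expected, so outside the 9.4 REC route; only 9.3 remains, with no deadline |

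In the last row the CI could still call a particular case unexpected, because 9.4 leaves that to the CI's opinion. Section 9.5 does not say when a listed event should be treated that way.

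**Step 3: compare the relatedness tests.**

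| Section | Test | Who decides | Deadline stated |
|---|---|---|---|
| 9.2 | *Possibly* or stronger | A medically qualified person | None |
| 9.3 | Caused by the trial intervention | Site PI | None |
| 9.4 | Related; for the REC, also unexpected | CI or designate | 24 hours to CI; 15 days to REC |
| 9.5 | Directly related to the study intervention or qualitative work | CI, ratified by TSC | None |

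An event graded *possibly* is related under 9.2 but may fail the tests in 9.3 and 9.5.

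**Step 4: place the TSC step.** Section 9.5 adds ratification but does not say whether classification or reporting may go ahead first. Section 9.4 has no TSC step before the REC report. The relation between ratification and the 24-hour and 15-day clocks is undefined.

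**Step 5: size.** The protocol gives no expected rate of serious psychological events, so the number affected cannot be calculated.

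**The case against.** The strongest reply is that the exempt item is *fluctuation in self reports*, not serious deterioration. Suicidal ideation appears in a separate paragraph, and neither it nor hospital admission is on the exempt list. On this view 9.5 only keeps ordinary symptom variation from being reported under the discretionary important-medical-event part of 9.1. Section 6.1.2 also excludes people with a history of suicidal ideation or hospitalisation for depression. Section 9.6.1 adds participant and GP alerts at a TFI of 180 or more and a call at 4 weeks.

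That reading is possible and may be what was intended, but the text does not say it. Section 9.4 shows that an exemption can be given a clear edge: it excludes elective admissions for a pre-existing condition. Section 9.5 has no such edge. The 9.6.1 safeguards protect the participant but do not replace SAE reporting to the CI and Sponsor.

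Three stronger readings are tempting, and the protocol does not support them:

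- *Reporting waits about six months for the TSC.* Nothing says that the judgement or the report waits for ratification. The 9.4 REC report rests on the opinion of the CI or a designate, the meeting frequency in 14.3 is a minimum, and SAEs may be referred to the TSC without reference to a scheduled meeting. No length of delay can be derived.
- *The between-arm adverse event comparison is understated.* That secondary outcome counts AEs to 3 months. An event that loses SAE status is still an AE and still counts.
- *A related event never reaches the REC.* Section 9.3 remains as a route if the site PI judges the event caused by the intervention. What it lacks is a deadline and a test consistent with 9.2.

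**Conclusion.** The contradiction is real and lies in the current text. For a serious event described as tinnitus-related mood change and judged unrelated, 9.1 with 9.4 requires SAE handling and 9.5 removes it. The loss is of SAE recording, the 24-hour CI report and Sponsor notification; AE collection to 3 months remains. Three further defects follow: inconsistent relatedness tests, a related-but-expected event left with only an undated REC route, and a ratification step with no stated timing.

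The conclusion assumes that a serious mood event could be described in the terms of the exempt item, which the wording permits but does not state. It does not bear on the primary outcome or its analysis. The case for correction is that safety staff cannot follow both rules at once.

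**What to change.** Amend 9.3 to 9.5 so that they agree with each other and with 9.1 and 9.2:

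- Limit the 9.5 exemption to events that do not meet any 9.1 seriousness criterion. Events that do meet one follow 9.4 whatever their presumed cause.
- Use the 9.2 categories wherever relatedness is judged, replacing the separate tests in 9.3 and 9.5, and name who decides.
- State that TSC ratification does not hold up SAE classification or any report.
- Align 9.3 and 9.4 on which events go to the REC and by when, including a related event of a kind listed as expected.

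The cost is a short protocol amendment and perhaps a few more SAE forms. No new procedure, visit or staff is needed, and participant care is unchanged.

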## 9.6 Measures to minimise the occurrence of AEs

### 9.6.1 Tinnitus Distress Monitoring

Participants will self-monitor their tinnitus related distress via the TFI at follow up intervals. Throughout the trial they will be asked to use the traffic light system (see Appendix 4) to ensure that they seek medical care as required. To further prevent any potential safety events, the central Lindus Health team will also monitor TFI scores at follow up visits and using the traffic light system (see Appendix 3), alert the participant and their GP to any TFI measurements which require follow-up (this is defined as any TFI score of 180 or above). All participants will also receive a phone call from a member of the clinical central trial team, 4 weeks after randomisation, to answer any queries and to specifically identify any potential issues relating to psychological distress.

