## 7.1 Digital Applications

For the duration of the trial participants will be asked to record their responses to questionnaires directly into the Lindus Health Electronic Data Capture (EDC) platform, via a participant survey link, which will be emailed and/or texted to them. The participants in the smartphone delivered CBT arm will also use the Oto tinnitus app. Certain fields may require duplicate data entry between the two digital systems, but it is essential that data on the Lindus Health platform is completed fully.

The Lindus Health team will have access to the EDC data and will review this on a daily basis (excluding weekends). Missing data will trigger an alert message to the participant via text/email. If no response is entered, a daily reminder will be triggered for 3 days, after which point the Lindus Health team will contact the participant to assess if they wish to withdraw from the study. If a participant wishes to withdraw then they will be advised to arrange an appointment with their GP or healthcare provider to discuss other treatment options (i.e. return to standard care), and a reason for withdrawal will be documented. Free access to the app will continue for participants in the Oto arm, or be offered free for 12 months from completion of the study for participants in the control group.

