## 7.7 Baseline Measurements (Day 1, up to + 7 days)

Once randomisation has been confirmed and prior to starting the intervention, participants will report baseline measurements in their survey which will include but not limited to:

- Complete information on previous treatment for tinnitus and costs already incurred e.g. over the counter supplements, hearing aids
- Complete TFI questionnaire
- Complete EQ-5D-5L and HUI3 questionnaires

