## 7.8 Administration of intervention

Following baseline data collection the participant will be granted access to either the trial intervention or control intervention. Access to the Oto app will be immediate. The first face-to-face CBT appointment will be scheduled within +/- 1 week.

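### The TFI alert at 180 or above is stated for follow-up visits only, so a baseline score that high triggers no stated action, and the gap is larger in the app arm

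*Protocol*

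**What the plan says.** Section 9.6.1 describes two uses of the TFI as a distress monitor, and both are tied to follow-up. For participants: "Participants will self-monitor their tinnitus related distress via the TFI at follow up intervals". For the trial team: "the central Lindus Health team will also monitor TFI scores at follow up visits and using the traffic light system (see Appendix 3"), after which the participant and GP are alerted to scores that need attention. The threshold is explicit: "this is defined as any TFI score of 180 or above". Separately, "they will be asked to use the traffic light system (see Appendix 4) to ensure that they seek medical care as required", and this self-use is to run for the whole trial. Finally, "All participants will also receive a phone call from a member of the clinical central trial team, 4 weeks after randomisation", partly to look for psychological distress.

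The first TFI in the schedule is the baseline form. Section 7.7 places it after allocation: "Once randomisation has been confirmed and prior to starting the intervention, participants will report baseline measurements in their survey". Section 7.8 then says of the intervention arm: "Access to the Oto app will be immediate". Section 7.1 states of the trial team: "The Lindus Health team will have access to the EDC data and will review this on a daily basis (excluding weekends"), but the only trigger it names is missing data.

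**The concern.** The alert is an absolute level, not a change from baseline. A participant who scores 190 at baseline and 190 at month 1 is flagged on the second form and not on the first, although nothing has changed. The protocol gives no reason for treating the two forms differently.

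The baseline form comes after the eligibility decision, so screening cannot respond to it, and it comes just before treatment begins. If nobody is assigned to act on it, a person reporting very severe tinnitus distress can start a self-directed programme with no response to that report until the next form. This is a safety-monitoring gap. It does not touch the validity of the primary comparison.

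**Working it through.** **1. Forms covered.** Section 4.1 and Appendix 2 schedule the TFI at baseline and at 1, 3, 6 and 12 months, which is 5 forms. Follow-up (section 7.10) comprises months 1, 3, 6 and 12, which is 4. Baseline has its own section (7.7) and its own column in Appendix 2. The alert therefore covers 4 of 5 forms. The synopsis gives the scale as 0 to 250, so the cut-off is 180/250 = 72% of the maximum.

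**2. Time from the baseline form to the first covered form.** Inputs: baseline on Day 1 with up to 7 days added (7.7); month 1 at week 4 with 7 days either side (7.10.1, Appendix 2).

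- Reading Appendix 2 as Week 4 Day 1 minus Week 1 Day 1: 3 × 7 = 21 days nominal.
- Reading month 1 as four full weeks: 28 days nominal.
- Shortest over the windows: 21 − 7 − 7 = 7 days. Longest: 28 + 7 − 0 = 35 days.
- Taking only the day-28 reading, with baseline on days 1 to 8 and month 1 on days 21 to 35: 21 − 8 = 13 to 35 − 1 = 34 days.

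Either way the interval is roughly 1 to 5 weeks. Against a programme of about 6 weeks (42 days, section 8.1), the nominal interval is 21/42 = 50% to 28/42 = 67%, and the extremes are 7/42 = 17% and 35/42 = 83%.

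**3. Does anything else act on the baseline score?**

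| Measure | Where | Stated to act on baseline TFI? |
| --- | --- | --- |
| Mental-health exclusions, applied on the screening call | 6.1.2, 7.4 | No; settled before the form exists |
| Adverse event review at baseline | Appendix 2 | No; no link to the TFI is stated |
| Weekday data review | 7.1 | No; missing data is the only named trigger |
| GP letter, and advice to ask the GP for an audiogram | 7.9 | No; they concern trial entry and hearing |
| Advice to seek help if mental state worsens | 9.5 | No; relies on the participant |
| In-app severity evaluation, optional chat | 7.6, 8.1 | No |
| Call at 4 weeks | 9.6.1 | No; made to everyone |

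**4. Difference between arms.** Section 8.2 starts control therapy within 1 week of randomisation. Section 7.8 schedules the first appointment within a week either side once baseline data are in, and baseline may itself be up to 7 days late, so 7 + 7 = about day 14 is possible. First therapist contact is thus at about 1 to 2 weeks. Appendix 3 has that assessment cover mental-health impact, with anxiety and depression questionnaires where appropriate, and requires an immediate phone call to the GP if self-harm risk is judged significant. For the app arm (196/2 = 98 participants), the first stated contact that looks specifically for distress is the call at 4 weeks.

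**5. Number affected.** The protocol gives no baseline TFI mean. Purely as an assumption, take normal scores with mean μ and SD σ, so that P(TFI ≥ 180) = 1 − Φ((180 − μ)/σ).

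| σ | μ = 100 | μ = 125 | μ = 150 |
| --- | --- | --- | --- |
| 31 (figure in 10.2) | 0.5% | 3.8% | 16.7% |
| 50 (assumed) | 5.5% | 13.6% | 27.4% |

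This is 0.5 to 26.9 of 98 app participants, or 1.0 to 53.8 of all 196: a range of about 50-fold (27.4/0.5), too wide to size the problem.

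**6. Traffic light tool.** Section 9.6.1 cites it once as Appendix 4 and once as Appendix 3. Appendix 1 is the flow chart, 2 the schedule, 3 the control-arm specification and 4 the amendment history. None of the 4 contains the tool.

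**The case against.** The best defence is that section 9.6 is about limiting events during the trial. A high baseline score is the presenting condition of people enrolled because tinnitus affects their lives, and treatment follows at once. Screening has also removed those with past suicidal ideation, psychiatric or psychological need beyond primary care, hospital admission for depression, or antipsychotic use. An adverse event review is scheduled at baseline, and everyone is advised at entry to speak to their GP. These are real mitigations and they lower the priority. They do not close the gap, because none responds to the score and the rule itself uses an absolute level.

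It can also be said that the threshold wording covers any score, and that the traffic light tool runs throughout the trial, so baseline may be covered after all. The threshold wording sits inside a sentence limited to follow-up visits, so the narrower reading is the likelier one. What the tool says about a baseline score cannot be known from the protocol, so the point is confined to what is stated.

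The contrast between arms can be pushed too far. Control contact may fall as late as about day 14, its questionnaires are discretionary, and it too is not tied to the trial's baseline form.

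**Conclusion.** The point stands as a modest safety gap. The alert covers 4 of 5 TFI forms, and a baseline score of 180 or more has no stated response for roughly 1 to 5 weeks. The gap is larger in the app arm, where no therapist session is planned in that interval. This rests on reading follow-up visits as excluding baseline, as the protocol's own section structure does.

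Three stronger readings might be inferred and are not supported:

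- **That severely distressed app users go unprotected for a month.** The exclusions, the baseline event review, the seek-help advice and the 4-week call all apply, and the interval can be as short as about a week.
- **That a sizeable share of participants is affected.** The number is unknown. The range shown above reflects chosen inputs, not trial data.
- **That the wrong appendix references disable the alert.** The threshold of 180 and the action are written in section 9.6.1 itself and work without the tool. The references are a minor error.

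**What to change.** Extend the sentence in section 9.6.1 so that the existing alert to participant and GP at 180 or above applies to the baseline form as well, by the same rule in both arms. As a minor correction, attach the traffic light tool as its own appendix and correct both references to it.

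The cost is a small protocol amendment and one flag on a form already collected, in a system already reviewed every weekday and already sending alerts for missing data. The price is some extra alerts at study start, in a number that cannot be predicted from the protocol. Some GPs may respond with early care, and section 8.3 prohibits no medication and permits hearing aids. Early additional care could blur a difference between arms in a non-inferiority comparison, so an effect on the primary result cannot be declared nil. Using one rule in both arms avoids building in a planned difference, and the medication and hearing-aid questions at month 1 (section 7.10.1) would help show whether care changed. The sample size and analysis method need no change.

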# 10. STATISTICS

The Statistician will be responsible for the statistical analysis, in accordance with the Statistical Analysis Plan. The SAP will be prepared separately, but an overview of the statistical methodology is provided here.

## 10.1 Description of Statistical Methods

The primary analysis will be conducted on the intention-to-treat (ITT) population. In addition to this, a per-protocol analysis will also be planned as a sensitivity analysis. Compliance will be defined as a minimum of 60 minutes of total use for the intervention group, and one or more sessions for the CBT group. Participants reporting poor compliance will be recorded and these participants will be included in the ITT analysis. Adherence to the smartphone app delivered programme will be monitored through the app with results analysed by intention-to-treat (ITT).

The primary outcome will be reduction in total TFI score at the 6 month point in the ITT population. Non-inferiority will be assessed by constructing a 95% confidence interval around the mean difference in TFI reduction between the groups, and comparing the -upper bound of the confidence interval to the pre-specified non-inferiority margin.

A secondary analysis of the primary outcome will examine significant differences between the control and intervention group’s TFI score at 6 months using a general linear model or a comparable suitable method, using the stratification variables and other potential confounding variables as covariates.

As a sensitivity analysis, the primary outcome will be analysed using the Per-Protocol (PP) population, which consists of participants complying with the treatment regimen. Compliance will be defined as a minimum of 60 minutes of total use for the intervention group, and one or more sessions of CBT for the control group.

Secondary outcomes will be compared between groups and over time with mixed-effects regression models for repeated measures, using the stratification variables and other potential confounding variables as covariates. Logistic models will be used for binary outcomes, and Gaussian models for continuous outcomes. An interim analysis may be conducted once a sufficient number of participants have completed the 6 month milestone. The results of the interim analysis do not influence the continuation of the trial.

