| Primary Outcome | Total TFI score (Score of 0-250 with high score indicating worse outcome) 6 months from starting therapy |
| Secondary Outcomes | 1) Total TFI and TFI subscale scores at 1, 3 and 12 months  2) Participant health-related quality of life measured using the EuroQol EQ-5D-5L and the Health Utilities Index Mark 3 (HUI3) responses and summary scores at 3, 6 and 12 months follow-up from starting therapy  3) Adverse events from randomisation to 3 months  4) System Usability Scale scores at 3 months  5) Qualitative feedback from focus groups and semi structured interviews at 3, 6 and 12 months  6) Cost-utility analysis synthesising costs and QALYs over trial period  7) Assess intervention adherence at 3 and 6 months |
| Number of participants | 196 participants, randomised in a 1:1 ratio |
| Eligibility criteria | Inclusion Criteria   1. Aged 18 years or over 2. Experienced tinnitus symptoms for at least 3 months and self-assessed as having a significant impact on quality of life. 3. Have access to a smartphone 4. Able and willing to give consent for the study prior to participation 5. Able to speak and read English to a sufficient level.   Exclusion Criteria   1. Tinnitus with potential “red flag” symptoms i.e. unilateral or pulsatile tinnitus (assessed via a red flag checklist during the screening call) 2. Significant mental health problems e.g. history of suicidal ideation or requirement for psychiatric/psychological support beyond Primary Care level 3. Have required hospitalisation for depression or taking antipsychotic drug 4. Currently taking part in another clinical trial for hearing/tinnitus 5. Awaiting surgical intervention for hearing/tinnitus 6. Previously undergone tinnitus therapy of any type e.g. CBT or TRT 7. Pregnant and breastfeeding women   Additional Note: Patients with hearing aids are eligible to participate in the study |
| Intervention | The Oto digital programme for tinnitus. This involves direct access to a digital multi-modal therapy package incorporating CBT, physical therapy, mindfulness and relaxation therapy. |
| Comparator | Current standard of care (1-1 therapist-delivered CBT). |
| Duration of study | 18 months |
| Randomisation / Blinding | Randomised 1:1 by computer algorithm and stratified by age, sex and level of hearing loss. Unblinded. |
| Statistical analysis | Non-inferiority |
| Intervention Adherence | Number of participants in each group completing therapy programme by 3 months |

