## 8.2 Control Group

Those allocated to the control arm of the study will undertake one to one tinnitus tinnitus therapy from a trained Audiologist/Hearing Therapist/Psychologist via video calls. This is not a direct mirror of NHS practice as patients will have rapid access to therapy, rather than typical long waiting times from GP referral. Participants in the control group will agree to not use Oto or an alternative tinnitus app for the duration of the study.

This control intervention will consist of a minimum of 1 tinnitus therapy session, with further sessions at the discretion of the participant and therapist up to a maximum of 6. Therapy will begin within 1 week of randomisation. There will be a panel of therapists selected to deliver the therapy. The therapy will include several elements of current standard care formulated into a personal management plan. :

- Assessment of participant needs
- Participant education
- CBT
- Relaxation therapy
- Signposting to hearing aid fitting and other support

In order to facilitate retention, participants in the control group will be offered the Oto Tinnitus Programme at the end of the 12-month RCT period.

Therapists will provide data to Lindus Health on attendance and number of sessions for each participant.

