## 10.2 The Number of Participants

The present study aims to show that smartphone app-delivered tinnitus therapy is not inferior to CBT in reducing tinnitus symptoms, assessed by the TFI score, after 6 months.

The required sample size was calculated based on a non-inferiority trial design with a non-inferiority margin of 13 points on the TFI scale, as used by two previous studies 9 10, and a standard deviation of 31 points. Assuming a power (1-β) of 90% and a significance level (α) of 2.5%, the sample size was determined as 90 participants per group. To account for a potential attrition rate of 10%, we increased the total sample size to 196 participants.

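### The primary non-inferiority rule has no coherent sign (difference in reductions, upper bound, unsigned margin, while the synopsis uses the score), and as worded it forgoes adjustment for baseline TFI and the strata

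*Protocol*

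**What the plan says.** Section 10.1 makes the primary outcome a reduction: "The primary outcome will be reduction in total TFI score at the 6 month point in the ITT population". It assesses non-inferiority by forming a 95% confidence interval for the "mean difference in TFI reduction between the groups, and comparing the -upper bound of the confidence interval to the pre-specified non-inferiority margin". Section 10.2 sets "a non-inferiority margin of 13 points on the TFI scale", without a sign. Neither section says which arm is subtracted from which.

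The synopsis defines the primary outcome differently: "Total TFI score (Score of 0-250 with high score indicating worse outcome) 6 months from starting therapy". The objectives table in section 4 also names the total TFI score at 6 months, for both the non-inferiority and the superiority objective. Section 3.2 speaks of change.

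Covariates first appear in the next paragraph of 10.1. It describes a secondary analysis of the 6-month TFI score, "using a general linear model or a comparable suitable method, using the stratification variables and other potential confounding variables as covariates". They appear again for the secondary-outcome models. They are not attached to the non-inferiority interval. Baseline TFI is collected from every participant (section 7.7, Appendix 2) but is nowhere named as a covariate.

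**The concern.** The sentence that decides the trial should admit one reading, and this one admits several. On the score scale a worse app gives a higher value. On the reduction scale it gives a lower value. Moving between the scales reverses the tail in which inferiority lies, so an upper-bound rule suited to one scale is wrong on the other unless the subtraction is reversed too. With scale, order and sign unsettled, the same data can support opposite conclusions. The trial is open label and 10.1 allows an interim analysis, so the direction should be fixed in writing before outcome data are seen.

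There is a second, smaller point. As worded, the primary interval is a difference in change scores, while the superiority analysis is an adjusted comparison of 6-month scores. One outcome is thus analysed on two scales with two estimators, and the one that decides the trial is the less precise.

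**Working it through.** **Inputs.** Margin 13, SD 31, one-sided α 2.5%, 90 per group, 196 in total with 10% attrition (section 10.2). The protocol does not say whether 31 is the SD of the 6-month score or of the change.

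**The plan's own figure.** n per arm = 2 × 31² × (1.960 + z)² / 13². With z = 1.282 (90% power) this gives 120. With z = 0.842 (80% power) it gives 90. The stated 90 per group therefore corresponds to 80% power, not the stated 90%. That is a separate matter, but it explains the power figures below. After 10% attrition, 196 × 0.9 = 176, or 88 per arm.

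**Which end of the interval is right**

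| Quantity | Inferior app gives | Correct test |
|---|---|---|
| Oto − CBT, 6-month score | positive values | upper bound < +13 |
| CBT − Oto, reduction | positive values | upper bound < +13 |
| Oto − CBT, reduction | negative values | lower bound > −13 |

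**Consequence under the third row.** At 90 per arm, SE = 31 × √(2/90) = 4.62 and the half-width is 1.96 × 4.62 = 9.06. Let D be the true reduction on Oto minus that on CBT. Then

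P(upper bound < 13) = Φ[(13 − D − 9.06) / 4.62]

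P(lower bound > −13) = Φ[(13 + D − 9.06) / 4.62]

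| D | Upper bound < 13 | Lower bound > −13 (correct) |
|---|---|---|
| −13 (Oto worse) | 0.9999 | 0.025 |
| 0 | 0.803 | 0.803 |
| +13 (Oto better) | 0.025 | 0.9999 |

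If the margin is instead given a minus sign and the upper bound need only exceed −13, an app 13 points worse still passes with probability 0.975.

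**Precision given up.** Assume equal variances at baseline and 6 months, and correlation r. The change-score variance is 2σ²(1 − r) and the ANCOVA variance is σ²(1 − r²), so the ratio is (1 + r)/2. The protocol gives no r; the values below are assumptions.

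If 31 is the SD of change, at 88 per arm:

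- Unadjusted: SE = 31 × √(2/88) = 4.67; power = Φ(13/4.67 − 1.96) = 79%.
- r = 0.5: SD = 31 × √0.75 = 26.85, SE = 4.05, power 89%.
- r = 0.7: SD = 31 × √0.85 = 28.58, SE = 4.31, power 85%.

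If 31 is the SD of the 6-month score, the number per arm for 90% power at r = 0.3, 0.5 and 0.7 is 168, 120 and 72 for change scores, against 109, 90 and 61 for ANCOVA. Any further gain from the stratification factors cannot be sized from the protocol.

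**The case against.** The strongest reply is that the protocol never writes Oto minus CBT. The upper bound is correct under two of the three readings, and one of these is the 6-month score that the synopsis and section 4 name. The aim of showing the app to be no worse is plain throughout, so a competent statistician is unlikely to run the perverse version. This stands: a reader might infer that the protocol tests the wrong bound, and the text does not prove that. It shows a rule whose scale, order and sign do not fit together. The stray hyphen before the word upper may be an editing or conversion remnant and carries no weight here.

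On covariates, section 10 calls itself an overview and leaves detail to a separate SAP. Baseline already enters through the reduction, and both estimators target the same effect under randomisation. This also stands in part. A change-score interval is valid, and the protocol does not forbid adjustment. What remains is that 10.1 does assign covariates, and assigns them only to the secondary models.

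A reader might also infer that the interval is too narrow because control participants share therapists: "There will be a panel of therapists selected to deliver the therapy" (8.2). The protocol gives neither the panel size nor the intraclass correlation, nor does it say that each participant stays with one therapist. If one assumes 5 to 15 therapists, correlations of 0.01 to 0.05, one therapist per participant and 90 per arm, ignoring clustering gives a one-sided error between about 2.6% and 5.0%. That range runs from negligible to important and rests wholly on assumptions, and such a term is commonly left to the SAP. It supports no finding of error.

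**Conclusion.** The point holds as an inconsistent, unsigned decision rule, and it needs correcting before any outcome data are analysed. The size of the harm depends on the reading. It is nil for Oto minus CBT on the score or CBT minus Oto in reductions, and a near-complete reversal of the trial's conclusions for Oto minus CBT in reductions. The probabilities assume normality, SD 31 and 90 per arm.

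The missing adjustment is a loss of efficiency, not of validity. It is worth roughly 6 to 10 percentage points of power at 88 per arm, provided that 31 is the SD of change, variances are equal and r lies between 0.5 and 0.7. The protocol states none of these.

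**What to change.** Replace the non-inferiority sentence in 10.1 with: *The primary estimate is the adjusted mean difference (Oto minus control) in 6-month total TFI from a linear model with baseline TFI and the stratification factors as covariates. Non-inferiority is concluded if the upper limit of the two-sided 95% confidence interval is below +13, and superiority if it is below 0.* Align the primary-outcome wording in the synopsis, section 4 and 10.1 with this, and state in 10.2 which SD the 31 is.

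With baseline TFI in the model, analysing the score or the change from baseline gives the same treatment coefficient, so the conflict of scales disappears and both objectives read from one interval.

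The cost is an amendment of wording. No new data are needed. As main effects, the strata in section 7.6 use 2 (age) + 1 (sex) + 6 (hearing) = 9 parameters, which about 176 participants can bear. A control-arm therapist effect may be added as a sensitivity analysis.
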